### Measures

#### Candidate mediators

*Prediction errors* will be measured via participant ratings of the probability of a negative event occurring; these ratings will be selected on screen via usage of the controller and are made after the onset of the CS^+^_P_, CS^+^_NP_, or CS^−^ but prior to the onset of the UCS.

*Attention* will be measuring using eye-tracking data (i.e., dwell time).

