### Hypotheses

Hypothesis 1: (a) Preexposure to a stimulus will lead to diminished prediction errors in the outcome of the pre-exposed stimulus and diminished attention to the target stimulus and (b) to decreases in fear acquisition, recall, and retention.

Hypothesis 2: Changes in prediction errors and attention will mediate the effects of preexposure on fear acquisition, recall, and retention.

Hypothesis 3: Higher pain sensitivity will be correlated with greater engagement of the targeted mechanisms and therefore, greater LI of fear acquisition, recall, and retention.

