### Experimental task

#### Overview

The experimental task will be presented in virtual reality, via the HTC Vive Pro headset [14] with programming done in Vizard [15]. Use of a novel immersive environment in virtual reality allows for the control of pre-exposure (i.e., stimulus novelty) and for the assessment of approach/avoidance behavior. The task will be presented as a game in which the participant is marooned on an unfamiliar planet (see Fig. 2). The goal of the game is to collect enough fuel to return home. Participants will be told that this planet works differently from Earth, the experiences they have on the planet and with its inhabitants may not follow the same rules, and that some of the interactions on the planet may be somewhat uncomfortable. These instructions are meant to activate schemas related to pain sensitivity, paralleling experiences at a dental visit, and they also provide a rationale for the mouthpiece that the participant wears during the experimental task.

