### Procedure

Although the participant will experience the “game” seamlessly, the task is broken up into four phases: pre-exposure, conditioning, and recall phases, administered during Visit 1, and a retention phase, administered during Visit 2. Each phase can be further broken down into a series of trials, which we describe next.

The *pre-exposure phase* consists of 12 trials. Each trial begins with a minimum of six seconds in which the participant is free to roam the planet using the HTC Vive Pro controllers to collect fuel hidden in the environment. At the completion of this phase of the trial an algorithm is set to deliver the CS^+^_P_, accompanied by a fuel canister, at the first opportunity.^2^ The CS^+^_P_ and the fuel canister will appear at a fixed distance from the participant. The CS^+^_P_ remains for the last six seconds of the trial. During pre-exposure, the CS^+^_P_ is never accompanied by the UCS.

The *conditioning phase* is made up of 36 trials (12 CS_P_^+^ trials, 12 CS^+^_NP_, and 12 CS^−^ trials) presented in a pseudo-random order. These trials follow the same structure as those in the pre-exposure phase with the exception that 75% of CS^+^_P_ trials, and 75% of CS^+^_NP_ are accompanied by a dental startle (described below). More specifically, the dental startle will be delivered during the last 100 ms of the trial, with the startle and alien co-terminating. The CS^−^ is never presented with the dental startle.

In the fear *recall phase* 12 trials (4 CS^+^_P_ trials, 4 CS^+^_NP_, and 4 CS^−^ trials) are presented. Again, these trials follow the structure described in the pre-exposure and conditioning phases; however, none of the aliens are presented with the UCS.

Fear retention will be assessed in the *retention phase*—a repeat of the recall phase administered a minimum of 7 days later.

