#### Indicators of fear learning

Data on subjective, behavioral, and physical indicators of fear learning will be assessed. Participants provide ratings of their state of relaxation/anxiety when in the presence of the CS^+^_P_, CS^+^_NP_, and CS^−^ periodically throughout the experimental task. Additionally, approach behavior will be quantified in two ways; the shortest distance between the participant and the CS^+^_P_, CS^+^_NP_, and CS^−^ will be recorded on each trial as will the data on whether or not the participant collected the “fuel cell” in proximity the CS^+^_P_, CS^+^_NP_, and CS^−^. Finally, skin conductance response to the CS^+^_P_, CS^+^_NP_, and CS^−^ presentations will be recorded using two Ag–AgCl electrodermal conductance electrodes with Isotonic gel placed on the middle phalanges of the non-dominant hand ring and pinky fingers. Data from the electrodes will be recorded using Biopac MP160 with a wireless BioNomadix module transmitter (Biopac Systems, California, USA.), with a sample rate of 2000 Hz, using Biopac’s Acknowledge 5.0 software (Biopac Systems, California, USA.). Skin conductance data will be analyzed based on prior work [16].

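### Same-trial dwell on the alien is tied to going for the fuel canister, so it cannot serve as mediator for fuel collection, and the pre-exposure fall in attention has no comparator

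*Protocol article*

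**What the plan says.** **Task.** The Overview of the experimental task states: "The goal of the game is to collect enough fuel to return home". Under Procedure, the pre-exposed alien is delivered "accompanied by a fuel canister, at the first opportunity"; the alien "and the fuel canister will appear at a fixed distance from the participant", and the alien "remains for the last six seconds of the trial". Only this alien is shown in the 12 pre-exposure trials. Of conditioning, Procedure says: "These trials follow the same structure as those in the pre-exposure phase", apart from the dental startle. Recall and retention keep that structure, so the canister accompanies all three aliens.

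**Mediator.** Under Candidate mediators, attention "will be measuring using eye-tracking data (i.e., dwell time". The Hypotheses section makes the object of attention explicit: "diminished attention to the target stimulus".

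**Outcome.** Under Indicators of fear learning, approach is scored on each trial by the shortest distance to the alien and by "whether or not the participant collected the" fuel cell close to it. The Analyses section names approach behaviour among the dependent variables.

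**Tests.** Hypothesis 1a in pre-exposure uses a one-way repeated measures ANOVA over trials and the mean change from first to last assessed trial. Hypothesis 2 uses multilevel mediation models with stimulus type, prediction errors and attention, and a z test of the indirect effect. No term for gaze on the canister is named.

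**The concern.** Gaze on the canister cannot also be dwell on the alien, and collecting fuel normally requires looking at it. Two analyses are affected.

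- **Hypothesis 2, fuel collection.** Mediator and outcome draw on the same seconds of gaze. The theory in the Introduction is that less attention means less fear learning, hence more approach. If dwell is scored on the alien alone and the canister takes gaze from it, low dwell goes with collection, which is the predicted pattern, even when attention plays no part.
- **Hypothesis 1a, pre-exposure.** Players who become better at going for fuel over 12 trials may look less at the alien without having learned that it predicts nothing. No second stimulus in this phase shows how much of the fall is practice.

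At stake is the claim that attention is a mechanism of latent inhibition, as far as it rests on these two analyses.

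**Working it through.** The article gives no gaze times, no dwell SD and no inputs to the power analysis, so there is no figure of the plan to reproduce. From the article: the six-second window, 12 trials per stimulus and 100 participants. All other inputs below are assumptions.

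**1. Pre-exposure trend.** Let collecting cost d = 0.5, 1 or 2 s of alien dwell, let collection rise from 50% to 80%, and let the SD of the change in dwell be 1 s apart from collection.

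- Fall in mean dwell = (0.80 − 0.50) × d = 0.15, 0.30, 0.60 s.
- Collection adds variance d² × (0.5×0.5 + 0.8×0.2) = 0.41d², if first and last trial are independent. SD of change = √(1 + 0.41d²) = 1.05, 1.19, 1.62 s.
- Standard error with n = 100 is SD/10. Fall/SE = 1.43, 2.53, 3.69.
- P(Z > 1.96 − fall/SE) = about 30%, 71%, 96%.

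Holding the SD of change at 1 s for every d would give 32%, 85% and 100%, but that ignores the variance that collection itself adds.

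**2. Same-trial correlation.** With collection on p = 60% of trials and a dwell SD of 1 s otherwise, the correlation of alien dwell with collection is −d√(p(1−p)) / √(d²p(1−p) + 1). For d = 0.5, 1, 2 this is −0.24, −0.44, −0.70, with no effect of attention on fear.

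**3. Indirect effect.** A simulation gave attention no causal role: 100 participants, two stimuli (pre-exposed or not), 12 trials each, 400 runs per setting. Collection became less likely as fear rose. Mean canister gaze was 1 s without collection, and 1 s plus the extra time shown with it. Alien dwell was a share of the remaining time, drawn independently of fear and stimulus. The indirect effect a×b was tested by z = ab / √(a²·SE_b² + b²·SE_a²), with standard errors clustered by participant. Pre-exposure either had no effect on fear or lowered it by 0.5 SD of trial-level fear by a route other than attention.

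| Extra canister gaze when collecting | Correlation, dwell with collection | Significant, no pre-exposure effect | Significant, effect by another route | Both paths with predicted sign, effect by another route |
|---|---|---|---|---|
| 0 s | 0.00 | 0% | 0% | 25% |
| 0.5 s | −0.19 | 3% | 13% | 81% |
| 1 s | −0.37 | 5% | 49% | 95% |
| 2 s | −0.65 | 5% | 86% | 100% |

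The last column counts the signs of the estimates whether or not they are significant.

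If canister gaze is instead counted as attention, the correlations become +0.19, +0.37 and +0.65 for 0.5, 1 and 2 s. The indirect effect is then significant in 16%, 45% and 88% of runs when pre-exposure acts by another route, and never with the predicted signs. The coupling stays and its direction reverses.

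The simulation has one mediator and a linear model for a binary outcome. It shows the mechanism and does not reproduce the planned Mplus models.

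**The case against.** **The scoring rule is not given.** Areas of interest are the kind of detail an article leaves to the full protocol or analysis plan, so their absence is no fault. This stands, and it means that the direction is not established. A reader might infer that the coupling must favour the hypothesis; the article does not support that. The fuel lies near the alien, so a collector has to turn towards it and might look at it more than a participant who avoids both. Gaze can also go elsewhere, and on some trials to on-screen ratings, so canister seconds need not all come from the alien.

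**The canister accompanies all three aliens.** This stands. It creates no difference between stimulus types by itself, and the stimulus-type contrasts in conditioning, recall and retention are not biased by its presence alone.

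**Goal-directed looking alone does not produce mediation.** A reader might infer that it does. The simulation says otherwise: with no pre-exposure effect on fear, rejection stays at about 5% or below. A pre-exposure effect by another route is needed. That case still matters, because Hypothesis 2 is meant to separate attention from other routes, with prediction errors as the rival.

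**A shift of gaze from an irrelevant alien to the goal object is what the theory predicts.** This is fair, and the rise in collection might itself come from learning that the alien is harmless. The pre-exposure test cannot tell this from practice at the game, and that is the limit of the point.

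**Same-trial pairing is not stated for Hypothesis 2.** True. The point applies where dwell and collection come from the same trials.

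**Conclusion.** The point holds in limited form. The article's own task places the goal object beside the alien in every stimulus window and scores its collection as an outcome that attention is meant to mediate. An attention-to-collection indirect effect is then uninterpretable if pre-exposure changes collection by another route. Under the assumed 0.5 to 2 s of extra canister gaze, a false indirect effect was significant in 13% to 86% of runs. The likely sign under alien-only scoring matches the prediction, but sign and size depend on the area of interest and the alien-canister spacing.

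In Hypothesis 1a only the pre-exposure trend is exposed, at about 30% to 96% for the assumed costs and the assumed rise in collection. These figures are ranges under assumptions and not estimates for this study. Fear ratings and skin conductance are not mechanically tied to canister gaze; minimum distance probably is in part.

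**What to change.** 1. From the existing eye record, score the canister as its own area of interest in every phase.
2. In the pre-exposure test, report canister dwell and collection by trial beside alien dwell. A fall in alien dwell matched by a rise in canister dwell should not be read on its own as learning that the alien is followed by no event.
3. Do not use same-trial alien dwell as mediator for fuel collection. Keep it for fear ratings and skin conductance, and interpret distance with caution. This removes the coupling from the mediation analysis of collection, whatever its sign.

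Do not redefine attention as alien dwell divided by the time not spent on the canister. Suppose gaze is first 3 s alien, 2 s canister and 1 s elsewhere: the share is 3/(6−2) = 0.75. If it becomes 1 s alien and 5 s canister, the share is 1/(6−5) = 1.00, so a clear loss of attention is scored as a gain.

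The cost is some re-scoring, provided the eye record locates gaze on the canister, plus a sentence or two in Measures and Analyses and one dropped mediator-outcome pair. Task, visits and sample size are unchanged. The choice should be fixed before the gaze data are analysed.

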#### Indicators of fear learning

Data on subjective, behavioral, and physical indicators of fear learning will be assessed. Participants provide ratings of their state of relaxation/anxiety when in the presence of the CS^+^_P_, CS^+^_NP_, and CS^−^ periodically throughout the experimental task. Additionally, approach behavior will be quantified in two ways; the shortest distance between the participant and the CS^+^_P_, CS^+^_NP_, and CS^−^ will be recorded on each trial as will the data on whether or not the participant collected the “fuel cell” in proximity the CS^+^_P_, CS^+^_NP_, and CS^−^. Finally, skin conductance response to the CS^+^_P_, CS^+^_NP_, and CS^−^ presentations will be recorded using two Ag–AgCl electrodermal conductance electrodes with Isotonic gel placed on the middle phalanges of the non-dominant hand ring and pinky fingers. Data from the electrodes will be recorded using Biopac MP160 with a wireless BioNomadix module transmitter (Biopac Systems, California, USA.), with a sample rate of 2000 Hz, using Biopac’s Acknowledge 5.0 software (Biopac Systems, California, USA.). Skin conductance data will be analyzed based on prior work [16].

#### Moderator

*Pain sensitivity* will be measured using a behavioral task – the cold pressor test as well a self-report measure- the Fear of Pain Questionnaire III [17] in participants 18 years of age or older and the Fear of Pain Questionnaire, Child report in participants up to age 17 years [18].

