**Methods:**

Healthy volunteers between the ages of 6 and 35 years will be enrolled across two sites. Participants will complete a conditioning task in a novel virtual reality environment, allowing for control over pre-exposure and the examination of behaviour. A dental startle (a brief, pressurized puff of air to a tooth) will serve as the unconditioned stimulus. Using a within-subjects experimental design, participants will experience a pre-exposed to-be conditioned stimulus, a non-pre-exposed to-be conditioned stimulus, and a neutral control stimulus. Two hypothesized mechanisms, changes in prediction errors and attention, are expected to mediate the association between stimulus condition and fear acquisition, recall, and retention. To ascertain the involvement of pain sensitivity, this construct will be measured through self-report and the cold pressor task.

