## Methods and analyses

### Participants and setting

Participant enrollment will occur at two university sites—one in northwest Ohio and one in south Texas. Based on a power analysis, we aim to recruit 100 participants from the general community, ranging in age from 6 to 35 years old. Full eligibility requirements are presented in Table 1. Participants will complete two in-person study visits and receive a $50 gift card at each visit completed.

**Table 1 Tab1:** Participant eligibility criteria

Inclusion criteria	Exclusion criteria
Be between the ages of 6 and 35 years old	Currently have glasses or use contact lenses with a vision correction of ≥ ± 6
At least 2 of their maxillary anterior 6 teeth present	Are colorblind
All of their maxillary anterior 6 teeth are stable	Current injury (including fractures, open cuts, or sores) on their dominant hand
All of their maxillary anterior 6 teeth are free of cavities	Fixed dental or orthodontic appliance that would interfer with creating a mouthpiece
All of their maxillary anterior 6 teeth are free of hypersensitivity to pain or pressure	Diagnosis by a dental/oral health professional of Temporomandibular Disorder (TMD) along with a history of exacerbation of symptoms resulting from routine dental procedures
Able to read, write, and converse in English (English or Spanish at Texas site)	Currently on any anti-anxiety or anti-depressant medications
Willing and able to provide a signed and dated informed consent/assent form to participate	Currently have an inner ear infection
Willing and available to comply with all study procedures and available for the duration of the study	Living in the same household or an immediate family member of an enrolled participant
	Currently have a cardiovascular disorder or a pacemaker
	Currently have a seizure disorder or epilepsy
	History of frostbite or sensitivity to extreme cold
	Bleeding disorder or take blood thinners
	Vasospastic disorder such as Raynaud's syndrome or Raynaud's disease
	Gastrointestinal or vestibular disorders that may elevate susceptibility to nausea and dizziness such as Meniere's disease, hyperemesis gravidarum or severe migraines
	Negative outcome with VR simulation
	Medical or psychological condition that requires them to avoid mild stress
	Any medical condition that elevates risk of falls, dizziness, nausea, or causes a vasovagal reaction
	Any other general or oral health concerns

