Inasmuch as learning effects cannot be seen until the conditioning phase, this hypothesis is tested only during the conditioning, recall, and retention phases. To test hypothesis 1b, the conditioning phase and recall and retention phase analyses described above will be conducted with indicators of fear learning (fear ratings, approach behaviour, and skin conductance response) serving as the dependent variables. In cases in which there are multiple measurements (i.e., fear ratings, skin conductance) scores will be averaged within each phase.

Hypothesis 2: Changes in prediction errors and attention will mediate the effects of pre-exposure on fear acquisition, recall, and retention.

To test the second hypothesis, three sets of multilevel mediation models [19, 20] will be estimated to test for mediation of the fear acquisition, recall, and retention effects. Each mediation analysis will include stimulus type (dummy-coded) and the two candidate mediators—prediction errors and attention.

Parameters will be obtained by maximum likelihood estimation with robust standard errors, a procedure that is robust to violations of normality and heteroscedasticity and obtains optimal parameter estimates when response data are incomplete [21, 22], with indirect effects tested by a z test. However, given the z test may be underpowered, we will double-check results by also using Bayesian estimation, which provides for improved inference via 95% credible intervals for indirect effects [23, 24].

Hypothesis 3. Higher pain sensitivity will be associated with greater engagement of the targeted mechanisms and greater LI of conditioned fear acquisition, recall, and retention.

To test the third hypothesis, individual differences in pain sensitivity will be included in the above analyses as a moderating variable.

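### Hypothesis 3 needs an age-group term: the pain questionnaire changes version at 18, and the moderation models name neither age nor version in a sample aged 6 to 35

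*Protocol article*

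**What the plan says.** Participants and setting: the planned sample is 100, said to rest on a power analysis, with participants "ranging in age from 6 to 35 years old".

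Measures, Moderator: pain sensitivity has two measures. One is the cold pressor test, for which no age split is stated. The other is a questionnaire whose version depends on age: "the Fear of Pain Questionnaire III [17] in participants 18 years of age or older and the Fear of Pain Questionnaire, Child report". The second of these is for everyone aged 17 or younger. The abstract confirms the two kinds of measure: "this construct will be measured through self-report and the cold pressor task".

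Study design and overview of procedures: pain sensitivity is the only measured subject variable listed. Age is not among the study variables.

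Analyses: the repeated-measures ANOVAs have trial, stimulus type or both as factors. The mediation models contain dummy-coded stimulus type and the two candidate mediators. For Hypothesis 3, "individual differences in pain sensitivity will be included in the above analyses as a moderating variable". No age or questionnaire-version term appears in any of these models, and no rule is given for putting the two versions on one scale.

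**The concern.** Every minor completes one version and every adult the other, so a shift in score at 18 may come from the instrument, from age, or from a real difference in pain sensitivity. The data cannot tell these apart.

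Stimulus type is varied within person, which protects the average stimulus effect from age. It does not protect a moderator that is measured between persons and not randomised. If children and adults differ both in their score and in the size of latent inhibition, a model without age credits part of the age difference to pain sensitivity. It can also do the reverse and hide a true moderation when the two differences run in opposite directions.

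The Discussion hopes the results will indicate who would benefit most from prevention programmes. An unadjusted interaction could not separate pain-sensitive people from children.

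**Working it through.** The plan has no figure to reproduce on this point. The sample of 100 is said to rest on a power analysis, but its inputs are not printed.

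**Inputs from the article:** n = 100; ages 6 to 35; questionnaire version switches at 18.

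**Assumptions, because the article gives no values:** two-sided alpha 0.05; share of minors p = 0.5 or 0.3; score offset between versions or ages d, in SD; minor–adult difference in the latent-inhibition contrast g, in SD; raw scores pooled with no age term.

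**Model.** Score S = pain + d × minor. Contrast Y = g × minor + noise, so pain has no true effect. The correlation induced between S and Y is

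r = d·g·p(1−p) / √[(1 + d²p(1−p))(1 + g²p(1−p))].

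The chance of rejection by Fisher z is Φ(δ − 1.96) + Φ(−δ − 1.96), with δ = atanh(r)·√97.

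**False moderation, g = 0.5:**

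| p | d | r | δ | Analytic | Simulated (4,000 runs) |
|---|---|---|---|---|---|
| 0.5 | 0.5 | 0.0625/1.0625 = 0.059 | 0.58 | 8.9% | 8–9.5% |
| 0.5 | 1 | 0.125/√(1.25 × 1.0625) = 0.108 | 1.07 | 18.9% | 17–19% |
| 0.5 | 1.5 | 0.1875/√(1.5625 × 1.0625) = 0.146 | 1.44 | 30.3% | 31% |
| 0.3 | 1 | 0.105/√(1.21 × 1.0525) = 0.093 | 0.92 | 15.1% | 14–16% |

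The ranges come from separate simulation runs. If d = 0 or g = 0, the formula gives r = 0 and the rate is 5%. Simulation gives 4.5–5.4%. Both differences are therefore needed for false positives.

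**Power, true r = 0.30, g = 0, p = 0.5.** The offset only adds noise, and the correlation becomes 0.30/√(1 + d²/4).

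| d | Attenuated r | Analytic power | Simulated power |
|---|---|---|---|
| 0 | 0.300 | 86% | 86–87% |
| 1 | 0.268 | 77% | 78% |
| 1.5 | 0.240 | 67% | 68% |

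**Masking.** With true r = 0.30, d = 1 and an age difference of 0.5 SD running against the offset, simulated power is 32%.

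**Under remedies, same simulations:**
- Adult/child group term: false moderation 4.4–6.0% in all settings. Power is about 86% when there is no age difference.
- Standardising within version, without a group term: 3.1–5.8%.
- Linear age term alone, on the raw pooled score: up to 16% in the worst setting (d = 2, g = 0.8, 30% minors).
- Standardising within version plus an age term: about 5% false positives and about 85% power.

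**The case against.** The strongest reply is that much of this is inferred. The article never says that raw scores from the two versions are pooled, nor that they are left unstandardised. Age-appropriate versions are not an error in themselves, and scoring rules and covariates are details that a condensed article often leaves to a fuller document. This stands in part: pooling is an assumption here, and the missing scoring rule is not the point. What remains is the model that the article does describe. It names one measured subject variable and gives the model terms in some detail, and none of them is age or version.

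A reader might also infer more than the article supports:
- **That all of Hypothesis 3 is confounded with instrument.** The version change touches the questionnaire only. No version split is stated for the cold pressor, where only the age concern applies.
- **That any child–adult difference would show up as pain moderation.** An overall age difference in gaze or skin conductance cancels within person. An age difference in cold-pressor tolerance alone creates no false interaction. The contrast itself must differ by age as well.
- **That the tests of pre-exposure are compromised.** The average stimulus effects in Hypotheses 1 and 2 rest on within-person comparisons and are not confounded by age.

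Finally, the sizes of d, g and p are not in the article. At a 0.5 SD offset the inflation is modest.

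**Conclusion.** The concern holds as a conditional weakness in the stated Hypothesis 3 analysis. Version and adult/child status are completely aliased, and the models described have nothing to separate pain sensitivity from age. Whether this yields false moderation, lost power, masking or no harm depends on two quantities that the article does not give: the score offset and the age difference in the contrast.

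With half the sample under 18, a 0.5 SD age difference in the contrast and pooled raw scores, the false-positive rate runs from about 8–10% to 31% as the offset goes from 0.5 to 1.5 SD. With no age difference in the contrast, the loss is power only: from about 86% to 77–78% at a 1 SD offset, or 67–68% at 1.5 SD, for a true r of 0.30. These figures illustrate the risk and do not predict this trial's results. The change is worth making because it is cheap and is most credible if settled before the data are seen.

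**What to change.** State in the Hypothesis 3 analysis that:

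1. the questionnaire score is standardised within version (mean 0, SD 1 among those under 18 and among those 18 and over);
2. every Hypothesis 3 model, including the mediation models, contains age group (under 18, 18 and over) and its interaction with stimulus type, next to the pain sensitivity terms;
3. the same terms are used when the cold pressor is the moderator;
4. a sensitivity analysis uses continuous age x stimulus type, since a two-level group leaves age variation within each group (6 to 17, 18 to 35) unadjusted.

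The article should also say how the two versions are combined.

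This changes analysis wording only. Age is already needed for eligibility and to choose the version, so no new data are collected. The price is a few degrees of freedom and no inference about child–adult differences in pain sensitivity, which standardising within version removes by construction. A site x stimulus term and separate moderation tests in minors and adults are not needed for this point, and the separate tests would be imprecise at this sample size.
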